### Monitoring

#### Safety monitoring

The 2015 South African operational guidelines on Ministerial consent for non-therapeutic health research with minors will be followed. We will categorise this study as non-therapeutic research because this is a phase I dose-finding, safety and PK study; we do not know whether the interventions, at the doses and intervals tested, will have therapeutic benefit. The following conditions will be applied:Condition 1: All consent will be provided by one or both parent/guardian who is the main person looking after the child. Consent procedures will follow GCP procedures, i.e. information sheets will be translated in vernacular language and routine care will not be affected by non-participation.Condition 2: The research may carry a risk as CAP256V2LS has not been tested in an infant population; however, CAP256V2LS is an antibody that was specifically derived from a South African adult patient; it specifically targets the strain of HIV pervasive in southern Africa and is highly potent. The trial with CAP256V2LS is initiated with available adult safety data of CAPRISA 012B [13]. Additionally, children will be closely monitored to ensure safety and document reactogenicity and adverse events.

Babies will be observed for a minimum of 2 up to 4 h after the first antibody dose and for at least an hour after the second antibody dose and will be reviewed face-to-face at days 1, 3, 14 and 28 post-delivery, then monthly up to month 6 post-delivery for babies receiving a single administration and up to months 3 for babies receiving the first bNAb administration and for additional 6 months post second bNAb administration for babies receiving two administrations. Additionally, study doctors and nurses will be available telephonically and in-person 24/7, to receive any calls or to see mothers and their babies face-to-face, in between these scheduled visit time points.

The first antibody dose will be given in a hospital setting (either within the RK Khan hospital or at the clinical research site which is located on the hospital precinct) to ensure close proximity to intensive care unit facilities and access to more than one paediatrician and nurses.

Furthermore, the Chatsworth CRS has community liaison staff, which would also be available in the community, directly or through the community advisory board to provide any support to mothers and their babies and to facilitate their access to immediate health care.

Lastly, through an existing memorandum of understanding with the R.K. Khan Hospital, any baby with any AE needing hospital-level care will be referred timeously. This will be facilitated by the fact that the Chatsworth CRS is on the premises of the R.K. Khan Hospital and within walking distance to the pediatric outpatient clinic and wards. Additionally, for this study, a research pediatrician will be employed on a full-time basis to complement existing staff and ensure the welfare of mothers and babies. This study pediatrician will oversee the safety of children and will work with existing clinicians at the site.

#### Toxicity management and enrolment in study arms

Arm 1 will follow a sequential recruitment, and all the other arms will be randomized. Simultaneous recruitment will occur for arms 2 and 4; arms 3 and 5; and will proceed as follows:

When the planned 8 infants of arm 1 have been enrolled, given study product and completed 28 days of follow-up, the study investigators will review interim safety data; there will be a 1-month pause in the enrolment and administration of subsequent doses (arms 2 and 4) during this review. If review of safety data reveals Grade 3 or higher AE possibly, probably, or definitely related to product administration, the study investigators will decide to consult with the ISMC. If review of safety data reveals no SAE, enrolment into subsequent dose arms will be opened. The same work-flow will apply to arm 2 and 4, arms 3 and 5, and arm 6. Infants enrolled in arm 6 will be treated with a second administration of bNAbs after 3 months constituting arm 6b; these babies will be followed according to the criteria described in the following paragraph.

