#### Study design

The scheme below summarizes the 3 steps of the trial.

[figure not shown]

Step 1 will evaluate the safety (adverse events, AE) and pharmacokinetics (PK) profile of the bNAbs when given alone as a single SC administration at two (VRC07-523LS) or three (CAP256V2LS) increasing doses (in mg per kg body weight), respectively, within 96 h of birth, in breastfeeding exposed neonates born without HIV and receiving the standard-of-care (SOC) antiretroviral (ARV) prophylaxis. If all 5 arms of step 1 are completed with no SAEs at least possibly-related to bNAbs, the trial will proceed to step 2, involving the use of 2 bNAbs in combination (arms 6/6b). If step 1 shows no bNAb-related SAE(s), following doses of VRC07-523LS and CAP256V2LS then steps 2 and 3 will proceed, and will evaluate the highest dose that is well tolerated. The second dose (arm 6b) will be administered after 3 months, in breastfeeding exposed neonates born without HIV (Table 1). All mothers and infants will also receive SOC ARV prophylaxis.

**Table 1 Tab1:** Description of each study arm

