#### Statistical methods

The statistical analyses of the PedMAb phase I trial will be performed, unblinded as to study arm, on the “safety analysis dataset” including infants who will have received at least one dose of the randomized bNAb (alone or in combination) and who have either presented a SAE grade 3–4 during the first 28 days following first or second bNAb administration or who have completed the same follow-up with safety assessment.

The analyses will be also performed according to the per-protocol (PP) principle. The PP analysis dataset will comprise infants who have received the expected dose(s) of the randomized bNAb (alone or in combination) and who have completed all their follow-up visits (6 months) since the first or second bNAb administration.

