#### Adverse events and serious adverse events

The mothers of exposed neonates born negative will be given and trained on using a standardised diary card to note any reactions at the injection site(s) and/or any AEs/SAEs that may occur after the bNAbs administration/s. Each AE and SAE that occurs during the study must be documented in the paper medical records (chart notes) of the patient in accordance with the standard clinical practice of the study investigators and on the AEs/SAE page of the e-CRF. A separate set of SAE pages must be used for each SAE.

The study investigators should try to formulate a diagnosis of the event on the basis of signs, symptoms, and/or other clinical information and record it on the AE and/or SAE pages. Similarly, with clinically significant abnormal laboratory values or other clinical examinations are consistent with the definition of an AE or SAE. It is important that the study investigators provide his/her judgment regarding the severity, expectedness, and potential relationship (causality) of the event to the study therapy on the initial SAE form.

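### The day-28 rule for opening the next dose arms has two branches that are not complements, and it differs from the Study design rule on unrelated SAEs; at version 4.0 the practical effect is small

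*Protocol article*

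**What the plan says.** The Protocol article states two rules for moving to the next dosing step.

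- **Toxicity management and enrolment in study arms.** Once the eight infants of arm 1 have completed 28 days, the investigators review safety data, and "there will be a 1-month pause in the enrolment and administration of subsequent doses (arms 2 and 4) during this review". Two branches follow. The first concerns a "Grade 3 or higher AE possibly, probably, or definitely related to product administration, the study investigators will decide to consult with the ISMC". The second reads "If review of safety data reveals no SAE, enrolment into subsequent dose arms will be opened". The procedure is then carried forward: "The same work-flow will apply to arm 2 and 4, arms 3 and 5, and arm 6". The section ends by referring arm 6b to the criteria in the next section.
- **Study design.** For the end of step 1 the condition is different: "If all 5 arms of step 1 are completed with no SAEs at least possibly-related to bNAbs, the trial will proceed to step 2". A later sentence extends it: "If step 1 shows no bNAb-related SAE(s), following doses of VRC07-523LS and CAP256V2LS then steps 2 and 3 will proceed".

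Two other places bear on what SAE means. Adverse events and serious adverse events has the investigators give their "judgment regarding the severity, expectedness, and potential relationship (causality) of the event to the study therapy on the initial SAE form". Statistical methods defines the safety dataset partly by infants "who have either presented a SAE grade 3–4 during the first 28 days", which attaches a grade to the term. The list of abbreviations expands SAE as serious adverse event.

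**The concern.** A rule that decides whether the next neonates are dosed should give one instruction for whatever the review finds. Here the consult branch depends on grade and relatedness, while the opening branch depends on seriousness alone. Seriousness, grade and causality are separate attributes, so the absence of one event is not the absence of the other.

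The event that meets both branches, a related Grade 3 AE that is not serious (a laboratory toxicity, for example), counts toward the primary endpoint. For that event the text calls for consultation and also permits opening, without saying which comes first. For an unrelated SAE it gives no instruction, while Study design would let the trial go on to step 2. At stake is whether a reader can tell from the protocol which findings hold the next dosing step and which release it.

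**Working it through.** The document gives no figure for this rule and no event rates, so there is nothing to reproduce and no probability is claimed. The check is a truth table.

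**Inputs.** Let S = serious, G = Grade 3 or higher, R = at least possibly related.

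- Consult the ISMC (Toxicity management): G and R.
- Open the next arms (Toxicity management): not S.
- Proceed from step 1 to step 2 (Study design): not (S and R).

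**Literal reading, one event seen:**

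| Serious | Grade ≥3 | Related | Consult | Open | Study design |
|---|---|---|---|---|---|
| yes | yes | yes | yes | no | does not proceed |
| yes | yes | no | no | no | proceeds |
| yes | no | yes | no | no | does not proceed |
| yes | no | no | no | no | proceeds |
| no | yes | yes | yes | yes | proceeds |
| no | yes | no | no | yes | proceeds |
| no | no | yes | no | yes | proceeds |
| no | no | no | no | yes | proceeds |

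Exactly one instruction: 4 kinds (row 1 and rows 6 to 8). Both: 1 (row 5). Neither: 3 (rows 2 to 4). 4 + 1 + 3 = 8. Study design proceeds where the opening condition is not met and no consultation is called for in 2 kinds (rows 2 and 4, the unrelated SAEs).

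**How far this depends on the meaning of SAE.**

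- If SAE means any Grade 3–4 event, the rules become: consult if G and R, open if not G. Of the 4 combinations of G and R, 3 have one instruction, none has both, and 1 (Grade ≥3, unrelated) has neither.
- If SAE is shorthand for the related Grade ≥3 AE in the preceding sentence, the branches are complements and all 4 have one instruction.

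**What other rules catch.** The pause in Analyses and stopping rules needs a related Grade 4 event, a death or life-threatening event, or two or more of eight infants in an arm with a related Grade ≥3 AE. The last trigger leaves out Grade 3 neutropenia, anemia and hyperbilirubinemia. A single related non-serious Grade 3 event does not trigger it.

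**Timing for arm 6b (Table 5).** The second dose is due on day 84 with a window of +7, so by day 84 + 7 = 91. If the eighth infant is dosed d days after the first, that infant's day 28 falls on day d + 28 of the first infant's clock. A review of the whole cohort at day 28 comes before the first infant's window closes only if d ≤ 91 − 28 = 63 days. With a 30-day pause added, d ≤ 91 − 28 − 30 = 33 days. The accrual rate is not stated.

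**The case against.** The strongest case is that little now turns on this wording.

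- **The step 1 decisions are spent.** Study design reports that data from arms 1 to 5 were adjudicated by the internal committee, the ISMC and the DSMB. This stands.
- **The opening branch concerns enrolment.** After arm 6 no further arm is enrolled: arm 6b is the same infants, and the section refers them to the arm 6b criteria. Those criteria withhold an infant's second dose after a Grade 3 toxicity of any cause until it improves and the investigators and ISMC approve. This stands too. A reader might infer that the protocol gives contradictory orders for the other infants' second doses, but that requires rewording an enrolment condition into a dosing condition.
- **The group decision is covered elsewhere.** The day-28 interim analysis in Analyses and stopping rules may adjust the second administration, and the committees can meet ad hoc. This largely stands, although that analysis waits for the last infant of the arm and names no event.
- **Both and neither are tolerable results.** Consulting and opening are not mutually exclusive, and where neither applies nothing opens, so the pause simply continues. A reader might infer that infants could be dosed after toxicity with no review. The documents do not support that, because the review itself always takes place. What stands against the objection is that opening is not said to wait for the ISMC's advice.
- **SAE may be loose shorthand.** Statistical methods attaches a grade to it, and the sample size section argues from SAE rates although the primary endpoint is a related Grade ≥3 AE. The reading is possible but not established. The abbreviation list gives the ordinary meaning, the adverse event section requires separate SAE pages, and both Study design and the stopping rules write out relatedness when they intend it.

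**Conclusion.** The rule is wrong as written, and the point is minor. On the ordinary meaning of SAE, the two day-28 branches overlap for one kind of event and leave three kinds without an instruction. The opening condition also disagrees with Study design on unrelated SAEs. These counts describe the logic only; they weight all kinds of event equally and measure no risk.

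The practical effect at version 4.0 is confined to arm 6. Table 2 requires a review of first-dose data before the second dose, and the same procedure is said to apply to arm 6, but that review has no single consistent trigger. The individual criteria for arm 6b, the any-time pause and the interim analysis all reduce what could follow from this. The conclusion rests on reading SAE as serious adverse event; if it was meant as shorthand for a related Grade ≥3 AE, the inconsistency within the day-28 rule disappears and only the wording needs correcting.

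**What to change.** Use one rule in both Study design and Toxicity management, applied in this order:

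1. Any event at least possibly related to study product that is Grade 3 or higher, or serious: hold the next dosing step until the ISMC has reviewed it.
2. Otherwise, any SAE: the investigators confirm and document that it is unrelated, with ad hoc ISMC consultation if in doubt, before proceeding.
3. Otherwise: proceed.

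Of the eight kinds of event, three fall under 1 (related and serious, Grade ≥3, or both), two under 2 (unrelated SAEs) and three under 3, so each has exactly one instruction.

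For arm 6b, apply the rule to the first-dose data available before each infant's second dose, in addition to the existing arm 6b criteria. It should not become a whole-cohort hold, so that the day 84 (+7) window is kept whatever the accrual.

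The cost is a few sentences in a protocol clarification, with no extra infants, visits or samples. The downside is a possible short delay for an ad hoc ISMC review, which Safety committees already allows. For an event by day 28, at least 84 − 28 = 56 days remain before that infant's second dose is due and 91 − 28 = 63 before the window closes; infants dosed earlier have less time.

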#### Toxicity management second administration – Study arm 6b

A second bNAbs administration will occur in arm 6b and should be provided according to the following criteria:In case of Grade 3 toxicities after the first bNAbs administration (regardless of their relationship to study product), the second dose should not be administered until after consultation with the study investigators AND improvement of the event to < Grade 3. After approval by the study investigators and the ISMC, the second administration may occur. If the event persists, no further administrations may occur.In case of Grade 4 toxicities considered as not related or possibly or probably not related, the second administration may occur after improvement to < Grade 3 and consultation with the study investigators and the ISMC. If the event persists, no further administrations may occur.

Subsequent administration should not occurIn case of any Grade 4 toxicities considered as possibly, probably, or definitely related to study product,.In case the infant has documented or suspected serious medical or immediate life-threatening condition at the time of the planned second bNAb administration.In case the infant is admitted in ICU or high care requiring supplemental oxygen at time of planned second bNAbs administration.In case an infant is determined to have acquired HIV after the first bNAb administration orIn the case of an infant who has stopped breastfeeding (before the second dose).

#### Adverse events and serious adverse events

The mothers of exposed neonates born negative will be given and trained on using a standardised diary card to note any reactions at the injection site(s) and/or any AEs/SAEs that may occur after the bNAbs administration/s. Each AE and SAE that occurs during the study must be documented in the paper medical records (chart notes) of the patient in accordance with the standard clinical practice of the study investigators and on the AEs/SAE page of the e-CRF. A separate set of SAE pages must be used for each SAE.

The study investigators should try to formulate a diagnosis of the event on the basis of signs, symptoms, and/or other clinical information and record it on the AE and/or SAE pages. Similarly, with clinically significant abnormal laboratory values or other clinical examinations are consistent with the definition of an AE or SAE. It is important that the study investigators provide his/her judgment regarding the severity, expectedness, and potential relationship (causality) of the event to the study therapy on the initial SAE form.

#### Safety committees

The Internal Study Safety Committee (ISSC) will review a safety report every 2 weeks, and meet monthly, or ad hoc when the need arises. The ISSC will include the three pediatricians on the study team, the site PI, the Sub-Investigator, the study managers and the Clinical Research Organization (CRO) representative.

An Independent Safety Medical Committee (ISMC) will meet every 6-months to review the safety data or ad hoc if there is a safety trigger. The ISMC is formed by 3 pediatricians and a neonatologist.

The Data and Safety Monitoring Board (DSMB) will review safety, PK and other data and will meet every 6-months or ad hoc if there is a specific need. The DSMB is an interdisciplinary group formed by 5 members (1 statistician, 1 virologist, 1 pharmacologist, 1 sociologist, 1 pediatrician).

Members of the ISMC and DSMB will be independent of study conduct and free of conflict of interest, and measures will be in place to minimize perceived conflict of interest.

The ISMC and DSMB will assess progress, safety endpoints and recommend whether the study should continue, be modified or halted.

#### Trial monitoring

An external CRO will be hired to conduct monitoring of all aspects of the trial as per GCP.

#### Analyses and stopping rules

Stopping rules have been defined and will be applied in order to protect the study participants from unnecessary exposure to the monoclonal antibody, should the safety profile prove unacceptable in this population. Unblinded interim exploratory (as this trial is proof-of-concept, no flexible alpha spending function approach will be employed) analyses are planned when the last infant of each study arm will have completed 28 days of follow-up since the first dose of bNAb(s) (individually administered or in combination). These analyses may lead to stop enrolment of subsequent dose arms, adjustment of doses or of the second bNAbs administration.

If at any time during the study, the following triggers are met:i)any of the infants dies or has a life-threatening adverse event or any Grade 4 event that is possibly, probably or definitely related to CAP256V2LS or VRC07-523LS administration;ii)two or more of the eight infants in each arm of the study have a Grade ≥ 3 adverse event at least possibly related to CAP256V2LS or VRC07-523LS administration (excluding Grade 3 neutropenia and anemia, and hyperbilirubinemia), the study investigators will pause the study for evaluation and will request that a DSMB review be performed within 7 days since the event occurrence. The DSMB will decide what additional data they would like to see and advise the study investigators on how to proceed. DSMB may decide on premature termination of some dose/arms (not of the trial); the decision may apply to either the CAP256V2LS or the VRC07-523LS arms (to each single dose/arm) and considers the occurrence in the CAP256V2LS arms independent of that in the VRC07-523LS arms. If the DSMB decides that further enrolment or administration cannot be continued, the study will stop accrual or administration but continue safety follow-up of all enrolled infants.

#### Missing data/loss to follow-up

All reasonable efforts will be taken to minimise loss to follow-up, which is expected to be minimal as data collection for primary and secondary endpoints. Contact details recording and tracking systems are in place to ensure a low rate of lost in the study; in addition, in the sample size calculation, we allowed for a 25% of loss to follow‐up. The number and percentage of participants with complete follow-up information at day 28 and at 6 months, since first or second dose of bNAbs administration (alone or in combination), will be reported.

## Ethics and dissemination

A rigorous ethical and regulatory approval process specified by the national and institutional regulation will be followed. SAHPRA (South African Health Products Regulatory Authority) notification of approval is required before participants can be enrolled in this study.

As per South African Good Clinical Practice Guidelines (SA-GCPs), the G-EthicsHR, and the G-GPHlthCare, the informed consent form (ICF) and patient information sheet(s) are essential documents that will be reviewed and approved by the SAMRC Human Research Ethics Committee (HREC), an accredited ethics committee (EC) based in South Africa and provided to SAHPRA with the clinical trial application.

Protocol amendments will follow the same procedure. The study will be implemented after consultation and buy-in from the Chatsworth CRS Community Working Group (CWG). These discussions commenced in 2020, and updates will continue throughout study implementation.

### Consent or assent

Written informed consent for study participation will be obtained before any study related procedures are performed. Mothers will be consented and screened prior to delivery or shortly after delivery of their infants, but randomization of the mother-infant pair will not proceed until the infant eligibility criteria have been confirmed. According to the SA-GCPs, the ICF and any patient information sheet(s) should be written in English and in the vernacular language that the participant is able to understand. Thus, we will provide information to the participants in a language that the participant understands and in a manner that takes into account the participant’s level of literacy, understanding, values, and personal belief systems. The Coordinator or a person designated by the PI will provide research study information to the participant and/or his/her legal representative(s), or guardian(s). The ICF content will be briefly and clearly presented, without coercion or unduly influencing a potential participant to enroll in the clinical trial. The original signed informed consent documents (ICF) will be retained by the investigator and a copy will be given to the participant for his/her record.

The current v4.0 dated 15 March 2024 Protocol, with its ICF and PIS, has been approved by SAHPRA and by the SAMRC HREC on Apr 23, 2024 (Appendices 2 and 3). Relevant changes to previous protocol versions are listed in Appendices 1.

The study has also been notified and approved by the Institutional Review Board of the Montpellier University Hospital, Montpellier, France on March 3, 2022; by the Ethics Committee of the San Raffaele Hospital, Milan, Italy on May 11, 2022; and by the Regional Committee for Medical and Healthcare Research Ethics (REK) north, Norway on December 12, 2022.

